#### Primary outcome measure

*Depressive symptoms: *The primary outcome measure was the Centre for Epidemiological Studies Depression scale (CES-D; [35]). This 20-item self-report scale was used to measure change in the severity of depressive symptoms.

#### Secondary outcome measure(s)

The following secondary measures were used at *baseline *and in at least one *subsequent *survey to evaluate improvement or change in mental health, other outcomes and potential moderating or mediating factors:

*Anxiety severity*: The Penn State Worry Questionnaire (PSWQ)[36]; *Quality of life*: The EUROHIS QOL - 8 item index [37]; *Disability: *'Days Out of Role' questions adapted from the US National Comorbidity Survey [38]; *Self esteem: *Rosenberg Self-esteem Scale [39]; *Perceived social support: *The 8-item Medical Outcomes Study Social Support Survey (MOS)/Emotional/informational support subscale [40]. This scale was considered more relevant than others to online as opposed to face-to-face or telephone support. *Loneliness*: The UCLA Loneliness Scale [41]; *Stigma*: Depression Stigma Scale (DSS-Personal), a measure of personal, negative attitudes to depression [15,42]; *Depression knowledge*: (i) a short 11-item version of the Depression Literacy Scale (D-Lit depression literacy scale; [15]); (ii) 33 depression treatment knowledge items evaluating the perceived helpfulness ('Helpful', 'Neither helpful nor harmful', 'Harmful', or 'Don't know') of three medications, five psychological treatments 21 lifestyle or alternative treatments and 4 formal and informal sources of help [8,43]; *Help seeking: *Participants indicated (Yes or No) which of the above medication, psychological, lifestyle and alternative treatments or activities they had used or people they had consulted for depression in the past 3 months [8,43]; *Empowerment: *Power-powerlessness subscale of the Empowerment Scale [44]. This scale was developed in conjunction with mental health consumers; *Perceived utility of the Internet*: Two questions assessed participant's beliefs about the utility of the Internet for preventing and understanding depression ("I am confident that people could learn skills for preventing depression from a website" (Yes, No); "I am confident that a website could help people understand depression better" (Yes, No)).

In addition, the following measures were employed at one or more points post-intervention with a view to assessing their experience of the program: *Satisfaction and perceived benefits/negatives: *Satisfaction with the interventions was measured using 10 previously employed self-report items (e.g., 'How useful was the website?' (Very useful, useful, Not very useful, Not at all useful)) together with a series of questions based on items developed in a UK study of depression ISG users [45] (e.g., 'The website helped me to discuss subjects that I felt unable to discuss elsewhere.' (Strongly agree, Agree, Neither agree not disagree, Disagree, Strongly disagree) and the Consumer Reports CRES-4 scale [46,47]; *Perceived negative effects *were measured with items specifically developed for the purposes of this study (e.g., 'Were any of the following a problem for you as a result of using the website? 'Feeling annoyed or upset by the comments made by other members on the board.' (Yes, No).); *Participation in healthcare*: A three item measure, modified from a study of a physical health internet support group [48] was employed at post intervention to assess participants' self-reported capacity to discuss treatments with their provider, feel in control and knowledgeable and be assertive with their healthcare provider; *Adherence*: measured in two ways for each individual: (i) completion of post-test surveys; (ii) number of modules completed (e-couch & Health Watch); (iii) frequency of logins and number of weeks logged onto the WellBeing ISG and activity level on each website (*e-couch*: number and percentage of exercises completed; number and percentage of pages downloaded; *WellBeing Board*: number of posts, number of threads started; HealthWatch: number and percentage of questions completed and pages downloaded).

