### Objectives of the ANU WellBeing study

The primary objectives of the study are to (i) evaluate the efficacy of a depression Internet Support Group (ISG) and an automated psychoeducational and skills Internet Training Program (ITP) for reducing depressive symptoms relative to a plausible Internet Attention Control condition (IAC); to evaluate the relative efficacy of the ITP, ISG and combined ITP and ISG interventions; and (iii) to ascertain if the adherence rates and magnitude of improvement in depressive symptoms is greater for the ISG and ITP interventions combined than for either condition alone.

Secondary objectives of the study are to (i) evaluate the effect of the two experimental interventions on anxiety, disability, social support, loneliness, self-esteem, empowerment, loneliness, depression literacy, stigma and help seeking in people with elevated depressive sympotms; and (ii) to compare the outcomes of these interventions in rural and metropolitan residents.

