### The Interventions

The study involved four intervention conditions comprising the two intervention programs presented singly and in combination and an attention-control website administered over a 12 week period. Although a module could not be accessed until the week scheduled for its delivery, it remained open for the remainder of the 12 week intervention period and for 12 months from the commencement of the intervention. Participants in the attention control condition were provided with access to the ITP after the 6-month follow-up assessment. The ITP, ISG and IAC conditions employed the e-couch, WellBeing Board and HealthWatch websites respectively. The weekly content of each intervention websites is summarised in Table 3 and described in detail below.

**Table 3 T3:** Summary of the WellBeing Trial topics for the intervention and control conditions.

	Condition		
	
Week	ITP: e-couch	ISG: WellBeing Board	IAC (Control): HealthWatch
1	Depression: What is depression? Risks & causes	How do you feel? (*Your WellBeing category*)	Environment *(Questions)* Environmental Health *(Information)*
2	Treatments: What works for depression	What helps? Who helps? (*Feeling Better category*)	Nutrition *(Questions)* Nutrition Myths *(Information)*
3	CBT: Thinking about thinking. (identifying thinking patterns that can lead to depression)	General chit-chat (*General category*)	Physical & Mental Activities *(Questions)* Maintaining a Healthy Heart *(Information)*
4	CBT: Changing your thinking (changing your thoughts to change your mood)	Do they understand? (*Your WellBeing forum*)	Physical Health *(Questions)* Energize Yourself (& Your Family) *(Information)*
5	CBT: Changing your behaviour (how to change your mood by doing things differently)	Positive things that happened to you today. (*Feeling Better forum*)	Social & Family Relationships *(Questions)* Medicines in the Home *(Information)*
6	CBT review (work on your workbook)	Jokes (*General forum*)	Travel *(Questions)* Temperature Extremes *(Information)*
7	IPT: Role disputes and relationships	Causes and triggers (*Your WellBeing forum*)	Education & Post Education *(Questions)* Oral Health *(Information)*
8	IPT: Role changes and grief	Your views on antidepressants & Connecting with others (*Feeling Better forum*)	Career & Work Relationships *(Questions)* Blood Pressure & Cholesterol *(Information)*
9	Physical activity (Part 1)	Creative corner (*General forum*)	Music & The Arts *(Questions)* Stroke *(Information)*

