#### ITP: E-couch (depression stream)

This automated online psychological intervention is a research version of the depression stream of the online application e-couch http://ecouch.anu.edu.au. The intervention comprised a depression literacy module together with five interactive self help tools designed to reduce depressive symptoms.

The depression literacy module contained information about the symptoms and types of depression and their diagnosis, sources of help, information about the prevalence and disability burden associated with depression, depression risk factors, and evidence-based medical, psychological and lifestyle treatments for depression based on updated systematic reviews and clinical practice guidelines. The self help module comprised online versions of treatments amendable to delivery online and known to be effective in face-to-face therapy, bibliotherapy or computerised or Internet delivery. These included: (a) cognitive behaviour therapy; (b) interpersonal therapy; (c) applied relaxation; and (d) physical activity. An example page from the research version of e-couch is illustrated in Figure 1.

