#### IAC: HealthWatch

In the absence of a suitable existing web-based attention control condition, the HealthWatch website was purpose built for the WellBeing trial. It comprised 12 modules, each consisting of two online components.

The first component involved a series of online questions probing factors potentially related to depression and wellbeing. This component was modified and extended to 12 modules from a previously reported 5 module telephone control condition [9,15,33]. For example, the introduction to the humour topic (Week 11) commenced with the explanation: "Some people believe that humour and laughter can prevent depression and increase the enjoyment of life. Today we would like to ask you to think about humour and whether it is important to your mood". This introduction was followed by a series of 16 multiple choice and open-ended questions: e.g., Do you enjoy telling jokes? (Responses: Yes, No, I can never remember any); How often do you tell jokes (Responses: Never, Rarely, About once a month, at least once a week, Most days); What is the funniest joke you can remember? (Open ended response); Overall do you think your moods are affected by humour?

The second component of the each weekly website module contained online information about a series of 12 topics related to wellbeing. The content in this component of the modules was adapted for Australian use from publications of the National Institute of Health and other US government sources which permit public use. Material was chosen which addressed topics relevant to wellbeing but which contained no or minimal information about interventions for depression or stress.

Participants were instructed to log onto the website each week to respond to the questions in first component of the module, and then to read the material in the second. An example page from HealthWatch website is shown in Figure 3.

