### Intervention Study Procedure

All participants who provided written consent were sent a user ID and password by automated email. A second automated email sent one week prior to the commencement of the intervention directed them to log onto the website to complete the online baseline survey.

Each of the four conditions was then delivered over a period of 12 weeks. Participants received a weekly automated email informing them when the next module of their program was available. Those who failed to log onto the module were sent an email reminder four days after the initial email. Those who failed to log in thereafter received a telephone reminder from their interviewer. The current week's module was only available after first completing the modules assigned in the preceding week or weeks.

At the end of the 12-week trial, an automatic email was sent to participants requesting that they complete the post-intervention survey. Reminders were sent according to the protocol employed at baseline. Further follow up using this protocol was undertaken at 6 months and 12 months after the commencement of the intervention. The flow of participants is shown in Figure 4.

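### The post-test help-seeking items look back over the whole 12-week intervention, so Yes answers in the e-couch arms can reflect use of the assigned program

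*Protocol article*

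**What the plan says.** The Objectives section lists the effect of the experimental interventions on "depression literacy, stigma and help seeking in people with elevated depressive sympotms" among the secondary objectives. Table 4 schedules help-seeking behaviours at baseline, post-test, 6 and 12 months.

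Under Secondary outcome measure(s), participants answer Yes or No for each listed medication, psychological treatment, and the "lifestyle and alternative treatments or activities they had used or people they had consulted for depression in the past 3 months". The list is the 33-item one used for treatment knowledge: "three medications, five psychological treatments 21 lifestyle or alternative treatments and 4 formal and informal sources of help". The individual items are not named.

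On timing, Intervention Study Procedure states: "Each of the four conditions was then delivered over a period of 12 weeks". It continues: "At the end of the 12-week trial, an automatic email was sent to participants requesting that they complete the post-intervention survey".

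On content, the e-couch section lists the self-help treatments as "a) cognitive behaviour therapy; (b) interpersonal therapy; (c) applied relaxation; and (d) physical activity". For the attention control, the HealthWatch section says: "Material was chosen which addressed topics relevant to wellbeing but which contained no or minimal information about interventions for depression or stress".

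The Interventions section says of each module that "it remained open for the remainder of the 12 week intervention period and for 12 months from the commencement of the intervention". It adds that control participants receive the ITP after the 6-month assessment.

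**The concern.** The question asks what was used, not what was sought outside the study, and nothing in the article tells the participant to leave out the assigned website. A participant in the ITP or combined arm who worked through the CBT or physical activity modules for depression could truthfully answer Yes to a matching item on that ground alone. The attention control and ISG-only arms do not receive e-couch during this period. A difference between arms on such items would then mix receipt of the randomised program with help seeking.

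The trial could report that an automated program increases help seeking when participants had only used that program. Program use is already recorded separately under adherence, so counting it again here would not help to answer the help-seeking objective.

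**Working it through.** The article gives no help-seeking rate or effect, so there is no stated figure to reproduce. Three checks apply.

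**1. Recall window against intervention period.** The intervention lasts 12 × 7 = 84 days. Three months is 365.25 / 4 = 91.3 days. A post-test survey completed when requested therefore looks back over the whole intervention.

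**2. Items against program content.**

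| Item category (count) | Delivered by e-couch? |
|---|---|
| Medications (3) | No |
| Psychological treatments (5) | Same category as CBT and interpersonal therapy (Table 3, weeks 3 to 8) |
| Lifestyle or alternative treatments (21) | Same category as physical activity and relaxation (Table 3, weeks 9 to 11) |
| Formal and informal sources of help (4) | Not by e-couch; board peers might be counted as informal |

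The counts add to 3 + 5 + 21 + 4 = 33. The overlap is between categories. Without item names it cannot be shown item by item.

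**3. Illustration of size, on assumed rates.** Consider one overlapping item. Let p0 be the share answering Yes because of help outside the program, equal in all arms. Let c be the share of the remaining e-couch participants who answer Yes because of the program. Then the e-couch arm shows p1 = p0 + (1 − p0) × c.

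With d = p1 − p0 and n = 125 per arm (the target), the chance of a two-sided 5% result is Φ[(d − 1.96 × se0) / se1]. Here se0 uses the pooled proportion and se1 the separate proportions.

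Example with p0 = 0.20 and c = 0.10:
- p1 = 0.20 + 0.80 × 0.10 = 0.28, so d = 0.08 and the pooled proportion is 0.24.
- se0 = √(0.24 × 0.76 × 2/125) = 0.0540.
- se1 = √[(0.28 × 0.72 + 0.20 × 0.80)/125] = 0.0538.
- Φ[(0.08 − 1.96 × 0.0540)/0.0538] = Φ(−0.48) = 0.32.

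| p0 | c = 5% | c = 10% | c = 25% |
|---|---|---|---|
| 5% | 9.8% v 5%: 30% | 14.5% v 5%: 72% | 28.8% v 5%: >99% |
| 20% | 24% v 20%: 12% | 28% v 20%: 32% | 40% v 20%: 94% |
| 40% | 43% v 40%: 7% | 46% v 40%: 16% | 55% v 40%: 66% |

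Each cell gives the e-couch arm against the comparator, then the chance of significance with no change in outside help. Both p0 and c are assumptions, and attrition is ignored. The artefact shows most easily when outside use is low. Table 2 excludes people in current CBT or in current or imminent treatment from a mental health professional, so low rates on the psychological items at entry are plausible.

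**Later assessments.** The 6-month window starts at about month 3, after the program ends, but modules are still open and controls do not yet have the ITP. At 12 months controls have had access to the ITP since the 6-month assessment, so they too may answer Yes because of e-couch.

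**The case against.** The strongest reply is that the overlap is inferred. The article names no items, and the questionnaire may tell participants to exclude the study website or may tie items to a provider. An article can fairly leave such wording to fuller documents. This stands, and it limits the point to what the measure can do as described. The sponsor holds the item list and can settle the matter.

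Second, no total or any-use score is fixed, and the grouping of items belongs to the analysis plan. This also stands. The omission is not the fault raised here; the point is that item-level answers, analysed as described, can credit program use.

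Third, the article's own definition includes treatments and activities used, so someone who takes up exercise through e-couch has changed the behaviour as defined. That is fair, and such uptake may matter as a mediator. It supports reporting uptake under its own name, not reading it as help sought.

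Fourth, the other arms are not free of related content. Table 3 gives the ISG topics on psychological therapy and on lifestyle approaches, and HealthWatch asks about physical and mental activities. This could reduce the contrast, but those arms do not receive the e-couch treatment modules in the intervention period.

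A reader might also infer that the contrast is certainly biased, or that an upward bias against the attention control persists to 12 months. The documents support neither. The first needs the item wording, and the second is undercut by control access to the ITP after 6 months.

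**Conclusion.** The point holds in a limited form. The post-test window covers the whole intervention, and the measure counts treatments in the same categories as those e-couch delivers. No stated rule excludes use of the assigned program. The contrast of an e-couch arm with the attention control or ISG-only arm can therefore be biased upward as a measure of help seeking.

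This rests on two assumptions: that some of the 33 items match e-couch content, and that some participants count the program when they answer. The size cannot be derived from the article; the tabulated figures only show that a modest share of such answers could be enough. At 12 months the direction of any bias against the attention control is unclear. Only a secondary outcome is affected, and the CES-D primary outcome is untouched. The change is worth making because it is cheap.

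**What to change.** For contrasts involving an e-couch arm, base the help-seeking conclusion on items that the assigned websites do not deliver: medications and formal sources of help. Keep informal sources separate where either arm has the peer board, since board members might be counted there. Report items that match e-couch content separately as use of strategies, or give a sensitivity analysis without them.

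Apply the same split at 6 and 12 months, and state with the 12-month results that control participants had access to the ITP after the 6-month assessment.

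The answers are already recorded by item, so no new data are needed; a short addition to the analysis plan is enough. The cost is that the help-seeking outcome rests on fewer items.

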#### Demographic and other measures

A number of other measures were collected in the screening survey. These included *demographic *data including gender, age, postcode, marital status, size of town of residence, level of primary and secondary education completed, current study being undertaken, and employment (status, main activity, usual job, past job). In addition, *severity of general anxiety, depression and stress *was measured using The Depression Anxiety Stress Scale (DASS-21; [49]), *social anxiety symptoms *were measured using the fear and avoidance subscales of the Brief Social Phobia Scale (BSPS; [50]) and *panic symptoms *were measured using The 5-item Patient Health Questionnaire (PHQ - Panic; [51]) scale. Participant *perceived mental health status *(stress, anxiety, panic, social anxiety, or depression), *self reported professional help seeking *for any such problem and *perceived usefulness of seeking professional help *for these problems were also collected. A series of purpose designed items were included in the screening survey to assess participant self reported *need for information about depression*. Finally, an item was included to measure participant *randomisation preference *at baseline.

### Planned data analysis and sample size

The WellBeing trial aimed to recruit and randomise 500 participants to four conditions (125 per group). The primary analysis will be undertaken on an intent-to-treat basis. Mixed-model repeated measures (MMRM) analyses will be used because this method has been demonstrated to be superior to using the last observation carried forward method for handling missing data in longitudinal designs [52]. For analyses of categorical outcomes, non-linear mixed modelling methods will be used. Based on previous studies, [8] we estimated pre-post effect sizes for the automated training program, the attention placebo and the ISG to be .6, .1, and .35 respectively. Power was set at 80% and calculations conservatively assumed a correlation of .5 between pre- and post-test measurements. Under these conditions the target sample size could detect a change from baseline of approximately .25 standard deviations in *a priori *contrasts of treatment arms conducted within the framework of omnibus test of condition by time mixed model repeated measures analysis. It is planned that the unique effect of the combined treatments will be tested by appropriate contrasts. It is possible that the combinations of treatment (e-couch and ISG) will prove no better than the individual programs. Conversely, cumulative effects or potentiation (synergy) may be observed. The target sample size ensured that the study is powered to detect an effect of .25 in either direction.

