#### Randomisation sequence

Potential participants were randomised using a stratified block design with stratification by level of psychological distress (high/low distress level on K10), gender (male, female, uncommitted), and location of residence (metropolitan/rural). Randomization schemes with a fixed block size of four were generated for each strata using the web site Randomization.com http://www.randomization.com.

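### The condition-by-time contrasts are planned on change from baseline; adjusting for baseline CES-D would cut their variance by 25% at the assumed correlation of .5, and by less if the correlation is higher or participants drop out

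*Protocol article*

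**What the plan says.** In the protocol article, Planned data analysis and sample size, the trial "aimed to recruit and randomise 500 participants to four conditions (125 per group". The primary analysis is intent-to-treat by mixed-model repeated measures. On power the section says "Power was set at 80% and calculations conservatively assumed a correlation of .5 between pre- and post-test measurements", and concludes that "the target sample size could detect a change from baseline of approximately .25 standard deviations". The comparisons to which this figure is meant to apply are pre-specified ones, placed by the section inside the "omnibus test of condition by time mixed model repeated measures analysis". The assumed pre-post effects are .6 for the training program (ITP), .35 for the support group (ISG) and .1 for the attention control (IAC).

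The section does not say whether baseline CES-D enters the model as a response or as a covariate. It names no covariates and excludes none.

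Under Randomisation sequence, allocation used "stratification by level of psychological distress (high/low distress level on K10), gender (male, female, uncommitted), and location of residence (metropolitan/rural"), in blocks of four. Participant recruitment describes three recruitment waves; wave is not listed as a stratification factor. The same section says that randomisation came before consent and before the pre-intervention survey, and that those who returned consent forms were then told their condition by letter. Intervention Study Procedure says that the baseline survey was requested by email one week before the intervention began.

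**The concern.** When baseline is an unconstrained time level, a condition-by-time contrast with complete data equals the between-arm difference in mean change. Its variance per person is 2(1 - r) in units of the CES-D variance. With baseline as a covariate the variance is 1 - r², which is smaller for every r below 1.

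The loss falls where the trial is weakest. The assumed effects put ISG against control at .35 - .1 = .25 SD and ITP against ISG at .6 - .35 = .25 SD. Both comparisons belong to the primary objectives, and both set 125 against 125. The gain needs no new data, because CES-D is already measured at baseline.

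**Working it through.** **Inputs.** From Planned data analysis and sample size: power 80%, r = .5, 125 per arm. From Table 1: factorial margins of 250 v 250. Assumed, because the article gives no figure: alpha .05 two-sided, no dropout (relaxed in step 4). The sum of the normal quantiles is 1.960 + .842 = 2.802.

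**1. The plan's own figure.** Change-score variance at r = .5 is 2(1 - .5) = 1.00. Detectable effect = 2.802 × √(2 × variance / n per side).
- 250 v 250: 2.802 × √(2/250) = .2506 SD, with 79.8% power at .25. This reproduces the stated .25.
- A within-arm change with n = 125 gives the same number: 2.802/√125 = .2506.
- 125 v 125: 2.802 × √(2/125) = .354 SD, with 50.7% power at .25. This does not reproduce it.

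Both routes that reproduce .25 use the change-score variance, so the planning is on the change scale.

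**2. Baseline as a covariate.** The variance is 1 - .5² = .75. The ratio to the change score is (1 - r²)/(2(1 - r)) = (1 + r)/2 = .75, a reduction of exactly 25%.
- 125 v 125: 2.802 × √(2 × .75/125) = .307 SD; power at .25 is 62.6%. Equivalent change-score sample: 125/.75 = 167 per arm.
- 250 v 250: 2.802 × √(2 × .75/250) = .217 SD; power at .25 is 89.8%.

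**3. Other correlations.** The reduction is (1 - r)/2.

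| r | change variance | covariate variance | reduction | power at .25, 125 v 125 (change → covariate) |
|---|---|---|---|---|
| .5 | 1.00 | .75 | 25% | 50.7% → 62.6% |
| .6 | .80 | .64 | 20% | 59.9% → 69.5% |
| .7 | .60 | .51 | 15% | 72.3% → 79.0% |
| .8 | .40 | .36 | 10% | 87.8% → 90.9% |

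These rows are for a contrast at one follow-up. If the contrast averaged three follow-ups with all correlations equal (assumption), the reduction would be 37.5% at r = .5 and 22.5% at r = .7.

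**4. Dropout.** In a mixed model with baseline as a response, participants with only a baseline still contribute. With n at baseline and m at follow-up, the per-arm variance is (1 - r²)/m + (1 - r)²/n, against (1 - r²)/m for the covariate form. With an assumed 30% loss (m = .7n):
- r = .5: .75/.7 = 1.071, and 1.071 + .25 = 1.321; reduction .25/1.321 = 19%.
- r = .7: .51/.7 = .729, and .729 + .09 = .819; reduction .09/.819 = 11%.

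**5. Strata and wave.** The article gives nothing from which the variance they explain could be derived, so no figure is attached to them.

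**The case against.** The strongest reply is that this is an efficiency preference, not an error. The change contrast is a valid estimator, the sentence on r is a power assumption rather than a model statement, and the article condenses a fuller plan that may already take baseline as a covariate. That stands in part: baseline as a time level is the natural reading of the condition-by-time test and the change-from-baseline effect size, but it is a reading.

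Four stronger inferences are tempting, and the article does not support them.

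- **That the gain is at least 25%.** The article calls .5 conservative, which implies an expected r of .5 or more. For a single follow-up, 25% is then nearer a ceiling than a floor for the baseline covariate, and dropout lowers it. To get back to 25%, strata and wave would have to explain a further 6.2% of the residual variance at r = .6 (1 - .75/.80) or 11.8% at r = .7 (1 - .75/.85). Nothing in the article shows that they do.
- **That the plan leaves out the randomisation strata.** The article is silent on covariates, and such lists are commonly left to a full protocol or SAP. If the strata were omitted, standard errors would err on the conservative side. Wave is a recruitment feature, not a stated stratum.
- **That adjustment costs nothing.** Baseline was requested after randomisation and, by the described sequence, probably after the condition was disclosed. It could therefore differ by arm through knowledge of allocation or selective consent. Change scores use the same baseline, so this does not favour them: a shift in baseline reporting passes fully into a change score and only in part into an adjusted contrast. A plain covariate model also drops randomised participants who have no baseline.
- **That adjustment repairs the power of the arm-versus-arm contrasts.** At r = .5 it reaches 63%.

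**Conclusion.** The point holds as an improvement in efficiency. On the natural reading, the planned contrasts are differences in change scores, and baseline adjustment is more precise for any r below 1. At the plan's r = .5, with complete data, one follow-up and two-sided alpha .05, variance falls by 25%. The gain shrinks to between 20% and 10% for r from .6 to .8, and to about 19% at r = .5 with an assumed 30% loss. It brings the 250 v 250 comparison from about 80% to 90% power at .25 SD. It does not bring 125 v 125 to 80% at r from .5 to .7; at r = .8 the change score already exceeds 80% unaided. Adding the randomisation factors is sound practice with an unquantified benefit, and the article does not show that they were omitted.

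**What to change.** State the primary model as follow-up CES-D on condition, time, condition × time and baseline CES-D × time. Include the randomisation factors as main effects: K10 (level or continuous), gender with the sparse third level pooled if it cannot be estimated, and location. The design has 2 × 3 × 2 = 12 strata, so main effects are safer than stratum cells. Recruitment wave may be added.

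State three things alongside it:
1. A sensitivity analysis that adjusts only for pre-randomisation screening scores (K10, DASS-21), because baseline probably followed disclosure.
2. How randomised participants without a baseline stay in the intent-to-treat set. A model that keeps baseline as a response with a common mean across arms is one option, but it assumes the equality at baseline that disclosure could disturb.
3. That the model was fixed before outcomes were compared by arm. Status of the Trial shows pilot and wave 1 through 12 months and wave 2 through 6 months, so the date of the decision should be recorded.

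The cost is analysis wording and one extra analysis; no new data are needed.
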